## Abstract

Body dissatisfaction is a core feature of eating disorders (EDs) and plays an essential role in the development and maintenance of anorexia nervosa (AN). In the current study, a computer based body exposure intervention is conducted and evaluated regarding short-term effects on body dissatisfaction, psychopathology, viewing patterns, and stress reactivity. Within a randomized controlled trial (RCT) female adolescents and young women with AN are either receiving the intervention or treatment as usual (TAU). Furthermore, in a transdiagnostic approach, a highly body-dissatisfied group of clinical control participants obtaining the intervention will be surveyed to identify AN-specific processes. The standardized four-session body exposure intervention using photographs of the own body is adapted from a manualized body image treatment program for computer use. Psychopathology (body dissatisfaction, body image avoidance, body checking, depression, anxiety) is assessed via standardized questionnaires before and after the intervention. During each session, attentional biases regarding one's own body are measured via eye tracking, stress levels are measured via subjective ratings, heart rate variability, as well as salivary cortisol and alpha amylase. Between- and within-subject effects will be assessed. The pilot study aims to identify short-term effects of the intervention on body dissatisfaction and attentional bias, as well as to investigate the potential underlying mechanism of physiological habituation.

## Introduction

Anorexia nervosa (AN) has a lifetime prevalence of between 0.5 and 2%, with a peak age of onset between 13 and 18 years (1). AN is characterized by abnormally low body weight, an intense fear of gaining weight, and a disturbed perception of the own body (2). AN is associated with poor outcomes: Mortality rates are high, and after treatment, less than one half of patients recover, whereas 20% remain chronically ill (3). Specifically, adolescent AN patients show high hospital readmission rates [45% after inpatient treatment (4)].

Body image (BI) is a multifaceted construct including perceptual, affective, cognitive, and behavioral components referring to the own and others' bodies (5). BI disturbances are diagnostic features and stabilizing factors in eating disorders (EDs): patients overestimate their shape and weight (6). Regarding behavioral aspects of BI disturbances, typical features in AN are body checking (repeated measuring and checking of shape and weight) and body avoidance [e.g., covering up the body shape by wearing baggy clothes or avoiding looking at oneself in the mirror (7)]. Despite much fewer studies on adolescents than on adults, a recent systematic review reported more BI disturbances in adolescents with AN and bulimia nervosa (BN) compared to healthy controls (8), similar to findings in adults. Alongside, Legenbauer, Thiemann (5) point out age-dependent differences between children, adolescents, and adults and the need for more studies for the still underresearched group of children and adolescents with eating disorders.

Disturbances of BI in EDs are thought of as a type of cognitive bias, with attentional bias (AB) being a form of biased information processing (9, 10). Evidence suggests that individuals with EDs demonstrate an AB regarding body shape-related stimuli, as examined by, e.g., the Stroop and Dot Probe task (11). ED patients not only show an AB for body-related information (i.e., words), but also for specific body parts (12). Especially, a bias toward negatively rated or most unattractive body parts was found in adolescents with eating disorders (13). This is in contrast to women without an ED diagnosis who showed a balanced attentional pattern regarding self-rated positive and negative body parts of their own body (14). Inducing a temporary AB for self-defined unattractive body parts leads to a significant decrease in body satisfaction in young women without EDs (15). This was confirmed by Tuschen-Caffier and colleagues (16) who found AB to be correlated with body dissatisfaction in women with AN and BN. In a previous study comprising of adolescent ED patients and a healthy control group, we assessed visual attentional processes via eye tracking while watching disease-specific pictures of female bodies (17). While all girls attended more to specific body parts (e.g., hips, upper legs), eating-disordered girls showed an AB toward unclothed body parts, which could be a behavioral marker for overestimation of shape and weight (17).

Based on the relevance of BI disturbances for the maintenance of EDs, it is crucial to target these explicitly (8). Particularly exposure interventions are highly recommended for ED treatment (8, 18, 19). Repeated body exposures in front of a full-length mirror (mirror exposure, ME), with patients wearing tight clothing or underwear to view the body shape and size as best possible, is a commonly used and recommended practice in ED treatment (20). This is applicable to both AN patients approaching a healthy weight and patients with BI disturbances without the diagnosis of AN (20). Former studies have shown ME as a one-time exposure or as part of a more comprehensive treatment program as being effective in the reduction of body dissatisfaction, body checking and body avoidance in adults (19, 21, 22) and adolescents (23) with AN or high body dissatisfaction. Besides ME, other body exposure interventions [e.g., exposure using video recording or virtual reality (24)] have been investigated and evaluated for treating patients with AN in a few studies, with cautiously positive results regarding improvement in BI facets (25). Altogether, evidence for body exposure interventions is still insufficient, especially for adolescent patients—results are mixed, and which patient groups benefit most from which form of body exposure, as well as the mode of action, are unclear (20, 25). Inter alia, modification of the AB and cognitive-affective habituation as along with habituation of physiological processes are discussed as potential underlying mechanisms (20).

Individuals with EDs (mainly investigated for BN) and highly body dissatisfied women show negative cognitive, emotional as well as altered physiological responses during the exposure to their own body [e.g., (26–28)]. For the assessment of stress reactivity, non-invasive measurements are typically used, e.g., heart rate (HR) and heart rate variability [HRV (29)] as sympathetic stress markers. These are affected by emotional stimuli (30) or stress (31). Studies have shown that individuals with AN have a consistently elevated HRV compared to healthy controls, which seems to normalize during recovery (32). Furthermore, salivary alpha amylase (sAA) is a marker of acute stress (33), highly correlates with blood norepinephrine levels (34, 35), and is thereby a further marker of the central sympathetic nervous system [SNS (36, 37)]. Lastly, cortisol, which is a correlate of an activated hypothalamic-pituitary-adrenal (HPA) axis, has been extensively investigated in EDs, showing both altered basal levels and reactivity (38). A study by Monteleone and colleagues (39) showed that individuals with AN exhibit an asymmetry between the HPA axis and the SNS response to a stressor, with the underweight AN group showing a strong cortisol reactivity but an almost completely lacking increase of sAA (comparable to the control groups).

While investigating stress reactivity to body exposure in women with BN who obtained six therapeutic sessions of ME, a decrease of salivary cortisol levels from the initial to the final intervention session was observed; this could be interpreted as habituation of the neuroendocrine stress response (40). Furthermore, a study in women with binge eating disorder found interactions between induced stress and body dissatisfaction during ME by measuring the biological response to social stress via salivary cortisol and sAA (41). Additionally, ED patients showed higher cortisol levels than control participants during a single 40-min body exposure task in a study exploring neuroendocrine (salivary cortisol) and physiological (skin conductance, heart rate) responses in women with EDs, compared to healthy controls. However, no group differences regarding neuroendocrine or physiological reactivity occurred (42). Investigating the effect of a three-session mirror exposure on psychophysiological sympathetic reactivity (HR, HRV, skin conductance) in women with BN vs. healthy controls showed an initial response within the sessions in both groups, but no physiological habituation between the sessions; thereby, the initial response was an unexpected decreasing sympathetic activity which might be explained by the stronger feelings of sadness compared to fear (28). So, until now, exact physiological mechanisms which go along with repeated body exposure in patients with AN or high body dissatisfaction are not yet clarified, with no study, to the authors' knowledge, investigating these in adolescents.

## Objectives

Due to the high association of BI disturbances and the development and maintenance of EDs, including AN, psychotherapy with patients with AN in any setting should include modules treating body image disturbances explicitly (8). A need for new, emerging treatments with a focus on brain-based interventions as well as mechanism-based approaches, which are specifically addressing psychopathology and BI disturbances, have been proclaimed (43, 44). While there is data available on the efficacy of body exposure interventions for reducing BI disturbances in women with EDs and high body dissatisfaction (20, 25), there is a lack of available data regarding the efficacy of body exposures with children and adolescents. Furthermore, different EDs are frequently mixed up in the literature, making it difficult to investigate specific processes, which might differentiate between body dissatisfied individuals with EDs and body dissatisfied individuals without EDs. Also, underlying psychophysiological and neurobiological processes during body exposure are still poorly understood. Therefore, the aim of this study is to investigate the short-term efficacy of a computer-based body exposure intervention for adolescents with AN. This group is being compared to an AN-TAU group and a body dissatisfied clinical control group.

The primary research question is: Is body dissatisfaction in adolescents with AN reduced after completing a four-session computer based body exposure intervention, compared to TAU?

Secondary research questions include: (1) Body checking and avoidance: Can four sessions of a computer based body exposure intervention reduce body checking and body avoidance behavior, compared to TAU? (2) Viewing patterns / attentional bias (AB): Can the AB in terms of focusing more on negatively rated body parts, measured via eye tracking, be reduced by a four-session computer based intervention in adolescents with AN, compared to TAU? Are there AN-specific AB modifications in comparison to a body dissatisfied control group also obtaining the intervention? (3) Stress reactivity: Do four sessions of body exposure modify stress reactivity in terms of a physiological habituation, measured via salivary cortisol, sAA, HR and HRV? Are there AN-specific effects in physiological habituation in comparison to a body dissatisfied clinical control group?

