### Design

Within a randomized controlled trial (RCT) female adolescents and young women with AN are either receiving four sessions of a computer based body exposure intervention (AN-INT) or treatment as usual (AN-TAU). Additionally, a highly body dissatisfied group of clinical control participants (CG-INT) are undergoing the intervention to identify AN-specific processes of the intervention. The study design, including study groups, time points and methods of assessment, is shown in Figure 1. The study includes intraindividual (pre- vs. post-intervention; modifications throughout the four exposure sessions) and interindividual (AN-INT vs. AN-TAU; AN-INT vs. CG-INT) research. The TAU group only completes the pre- and post-intervention sessions with assessment of psychopathology and a recording of gaze patterns.

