Until now and to the best of our knowledge, no study using a comparable computer based body exposure intervention using photographs of the own body could be identified. Because of this, sample size calculation for the current pilot study was performed in accordance with former studies assessing effects of mirror (body) exposure in adolescents and adults with EDs (23, 42), as well as fear-stimulus exposure in phobic adolescents (48), reporting mostly medium effect sizes for body avoidance (body) anxiety and negative emotions. According to sample size calculations [G^*^Power; (49)] based on default values (alpha error =.05, power =.80) and the assumption that effect sizes for the RCT (AN-INT vs. AN-TAU) are expected to be larger than for the comparison of AN-INT vs. CG-INT, both taking part in the same intervention, at least 23 participants are required for the intervention groups (AN-INT, CG-INT) and at least 15 participants are required for AN-TAU. This is calculated based on a 2 × 2-mixed design (RCT; between-subject factor: AN-INT vs. AN-TAU; repeated measure within-subject factor: pre, post) and a 2 × 4-mixed design (AN-INT vs. CG-INT; repeated measure within-subject factor: 4 exposure sessions), respectively.

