### Data Analysis

Research questions will be analyzed in repeated measures (rm)-AN(C)OVAs, considering within-subject and between-subject factors and interpreting—depending on the respective hypothesis—main and/or interaction effects. To test intervention effects on body dissatisfaction, body control and body avoidance, as well as AB comparing AN-INT vs. AN-TAU within the RCT, a 2 × 2-rm-AN(C)OVA (between-subject factor = group: AN-INT vs. AN-TAU; within-subject factor = time: pre, post) will be conducted. To assess modifications within and throughout the body exposure sessions regarding AB, emotion ratings, HR, HRV, as well as cortisol and sAA reactivity slope, a 2 × 4-rm-AN(C)OVA (between-subject factor = group: AN-INT vs. CG-INT; within-subject factor = time: 4 exposure sessions) will be conducted. Potential confounders are derived from a theoretical point of view (e.g., age, depression) and will be included as covariates in the statistical analyses (ANCOVAs). Specific test requirements will be tested prior to performing the full analysis. In case of non-adherence to the test requirements (i.e., normal distribution and variance homogeneity), the outcome measures will be logarithmized and additional non-parametric tests will be calculated. Data will be analyzed using IBM SPSS Statistics software. Significance level will be set at *p* =.05 and effect sizes will be interpreted. Effect sizes for AN(C)OVA results were computed as partial η^2^ ($\eta_{\text{p}}^{2}$), with values $\eta_{\text{p}}^{2}$ <0.06 interpreted as small,.06 ≤ $\eta_{\text{p}}^{2}$ <0.14 as medium and $\eta_{\text{p}}^{2}$ ≥ 0.14 as large effects (64). Correction for multiple testing will be applied if necessary.

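### The four-session outcomes are analysed by a method that discards partial records, and the wording of the primary question leaves open a completers-only reading of the intervention arm

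*Protocol article*

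**What the plan says.** All references are to the protocol article.

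- **Objectives.** The primary question is whether body dissatisfaction in adolescents with AN is "reduced after completing a four-session computer based body exposure intervention, compared to TAU".
- **Design.** Only the intervention groups have exposures to attend: "The TAU group only completes the pre- and post-intervention sessions with assessment of psychopathology and a recording of gaze patterns". AN-INT versus AN-TAU is the randomised comparison. CG-INT is an additional, non-randomised group.
- **Data Analysis.** "Research questions will be analyzed in repeated measures (rm)-AN(C)OVAs, considering within-subject and between-subject factors". The randomised comparison, covering the questionnaires and attentional bias, is a 2 × 2 model ("within-subject factor = time: pre, post) will be conducted"). The process outcomes for AN-INT versus CG-INT are attentional bias, emotion ratings, heart rate and its variability, cortisol and alpha amylase. They use a 2 × 4 model ("within-subject factor = time: 4 exposure sessions) will be conducted"). "Data will be analyzed using IBM SPSS Statistics software".
- **Procedure.** Questionnaires are repeated at a separate post-intervention session of about 10 minutes. AN-TAU has attentional bias recorded at the pre- and post-intervention sessions. For AN-INT, the only recordings described are the free-viewing periods at the start and end of each exposure session.
- **Target/Study Population.** At least 23 participants are required in each intervention group and at least 15 in AN-TAU, "based on default values (alpha error =.05, power =.80").

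**The concern.** Three separate matters meet here.

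1. **Method for the four-session outcomes.** The repeated-measures procedure in SPSS works on complete cases. A participant with three usable sessions out of four contributes nothing to that outcome. Each outcome needs usable data at four visits, so small losses per visit can accumulate.
2. **Wording of the primary question.** Only AN-INT has four exposures to complete. If the question were answered in completers, one randomised arm would be selected on an event after randomisation and the other would not. The Introduction reports negative emotional and altered physiological responses to viewing one's own body, so stopping may well be related to outcome.
3. **Attentional bias in the randomised comparison.** As described, the AN-INT end value comes from an exposure session and the AN-TAU value from the post-intervention session. Stopping exposures therefore removes the end value in one arm only.

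At stake are precision for the habituation questions and, for the randomised comparison, whether the estimate still describes the groups as randomised. The second also matters later, because the article intends the effect sizes to guide a larger multi-centre trial.

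**Working it through.** **Plan's own figure.** The minimum of 23/23/15 cannot be reproduced. The article gives alpha and power but no numeric effect size, no correlation and no tested term; it says only that former studies were "reporting mostly medium effect sizes for body avoidance (body) anxiety and negative emotions". Assuming the group-by-time interaction, correlation ρ = 0.5 and sphericity, the effect that gives 80% power with 46 participants in the 2 × 4 design is f = 0.175:

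λ = f²·N·m/(1 − ρ) = 0.175² × 46 × 4 / 0.5 = 11.27, on 3 and 132 degrees of freedom.

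This back-solved value serves only as the reference for the power column below.

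**Step 1: the 2 × 4 outcomes.** Let p be the share of values missing per session (assumed). With independent loss, the share of participants complete over four sessions is (1 − p)⁴. Among the values actually observed, the share discarded by complete-case analysis is 1 − (1 − p)³. The standard error grows by 1/√(share complete).

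| p (assumed) | Complete, (1 − p)⁴ | Of 23 per group | Observed values discarded, 1 − (1 − p)³ | Standard error × | Power (reference 0.80) |
|---|---|---|---|---|---|
| 2% | 0.98⁴ = 92% | 21.2 | 6% | 1.04 | 0.76 |
| 5% | 0.95⁴ = 81% | 18.7 | 14% | 1.11 | 0.70 |
| 10% | 0.90⁴ = 66% | 15.1 | 27% | 1.23 | 0.59 |

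If the same participants miss every session, the loss is only p. At 10% that leaves 20.7 of 23, and no model can recover anything because those participants have no session data. Reality probably lies between the two patterns.

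**Step 2: the primary questionnaire outcome.** The 2 × 2 model needs one pre and one post value. The post value is taken at a separate session, so a missed exposure deletes nobody. Only a missing pre value, post value or covariate does, and that can happen in either arm.

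**Step 3: what a completers-only reading would do.** Suppose, purely as an assumption, that those who stop gain nothing over AN-TAU. If k of 23 stop, the as-randomised effect is (23 − k)/23 of the completer effect, so the completer effect overstates it by the factor 23/(23 − k):

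- k = 2: 23/21 = 1.10
- k = 4: 23/19 = 1.21 (for example 0.50 SD against 0.5 × 19/23 = 0.41 SD)
- k = 6: 23/17 = 1.35

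Power would matter less. For 23 versus 15, 80% power corresponds to a standardised difference in change of 0.96. With 21, 18 or 15 AN-INT patients against 15, power for that difference is 0.78, 0.75 or 0.71. The issue under this reading is bias.

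**Step 4: does changing the model cure Step 3?** No. If those who stop supply post data, the existing 2 × 2 analysis already includes them and returns the as-randomised effect. If they do not, a pre/post mixed model assumes that their missing outcomes resemble those of comparable patients who stayed, and it would not recover a zero gain. Only collecting the post data does.

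**Step 5: attentional bias, arms side by side.**

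| | AN-INT | AN-TAU |
|---|---|---|
| Recordings described | Start and end of each exposure session | Pre- and post-intervention sessions |
| Effect of stopping exposures early | No end-of-course value, even if the post session is attended | Cannot occur |

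An AN-INT patient who stops is either dropped or represented by an earlier session.

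**The case against.** The strongest reply is that nothing in the article excludes non-completers. The wording in the Objectives may only describe timing: the secondary questions do not mention completion, the Design section uses the same verb for mere attendance by AN-TAU, and Strengths and Expected Outcomes restates the hypothesis as end against beginning of the intervention and against TAU. This stands. A completer analysis is a possible reading, not a stated plan. The absence of a named analysis set or missing-data rule is not a fault either, since a condensed article commonly leaves these to the full protocol or analysis plan.

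A reader might also infer that the primary analysis deletes anyone who misses a session, or that up to a third of the 2 × 4 sample will be lost. The documents support neither. Step 2 rules out the first. The second is 1 − 0.9⁴ = 34%, which presumes 10% independent loss per session; it is not a maximum, because 15% would give 48% and fully clustered loss at 10% would give 10%.

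It is fair, too, that 23 is a minimum and more may be recruited, that this is a small pilot of six sessions over about 2.5 weeks with a permanently assigned attendant, so losses may be low, and that the 2 × 4 comparison is not randomised, so its loss is one of precision and possible selection.

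What the reply does not meet is that the complete-case method is a stated choice with a better alternative in the same software, and that the recording scheme gives AN-INT a route to losing the attentional-bias end value that AN-TAU lacks.

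**Conclusion.** The point holds in three limited parts.

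- **2 × 4 process outcomes.** The stated method discards partial records. Under assumed independent losses of 2% to 10% per session, 92% to 66% of participants remain and standard errors rise by 4% to 23%; with fully clustered loss the reduction is only p. The power figures rest additionally on the back-solved f = 0.175 and ρ = 0.5.
- **Primary question.** The analysis as specified does not lose patients for missed exposures. The wording nevertheless permits a completers-only reading that would condition one randomised arm on a later event. The overstatement of 10% to 35% applies only under that reading, with 2 to 6 of 23 stopping and gaining nothing.
- **Attentional bias in the randomised comparison.** One-sided loss follows from where the recordings are taken. Its size cannot be given, because the article states no rate of early stopping.

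These are worth correcting before analysis. They do not show that the primary result will be biased.

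**What to change.** 1. **2 × 4 outcomes.** Replace the repeated-measures AN(C)OVA by a linear mixed model (SPSS MIXED, REML, small-sample degrees of freedom) with group, session and their interaction, using every available session. It assumes that missingness depends only on observed data, which is weaker than what complete-case analysis needs. With complete data little changes.
2. **Primary question.** Reword it to all randomised AN participants, compared by allocated arm. Report completers only as a secondary analysis, labelled as such.
3. **Data collection.** Invite every AN-INT participant to the post-intervention session regardless of exposures attended, and add an attentional-bias recording there where possible, so that both arms have an end value from the same visit. This step, not the change of model, guards the 2 × 2 comparison against completer bias.
4. **Any loss figures** quoted in planning should be labelled as assumptions and shown as a range.

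The cost is some analysis syntax in software already chosen, one short visit for those who stop early, a brief extra recording, and possibly a less favourable estimate.
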